# Effectiveness and cost-effectiveness of a physical activity loyalty scheme for behaviour change maintenance: a cluster randomised controlled trial

**DOI:** 10.1186/s12889-016-3244-1

**Published:** 2016-07-22

**Keywords:** Physical activity, Workplace, Intervention, Cluster RCT, Behaviour change maintenance, Financial incentives, Economic evaluation, Behavioural economics, Mediation analyses

## Abstract

**Background:**

Increasing physical activity in the workplace can provide employee physical and mental health benefits, and employer economic benefits through reduced absenteeism and increased productivity. The workplace is an opportune setting to encourage habitual activity. However, there is limited evidence on effective behaviour change interventions that lead to maintained physical activity. This study aims to address this gap and help build the necessary evidence base for effective, and cost-effective, workplace interventions.

**Methods/design:**

This cluster randomised control trial will recruit 776 office-based employees from public sector organisations in Belfast and Lisburn city centres, Northern Ireland. Participants will be randomly allocated by cluster to either the Intervention Group or Control Group (waiting list control). The 6-month intervention consists of rewards (retail vouchers, based on similar principles to high street loyalty cards), feedback and other evidence-based behaviour change techniques. Sensors situated in the vicinity of participating workplaces will promote and monitor minutes of physical activity undertaken by participants. Both groups will complete all outcome measures. The primary outcome is steps per day recorded using a pedometer (Yamax Digiwalker CW-701) for 7 consecutive days at baseline, 6, 12 and 18 months. Secondary outcomes include health, mental wellbeing, quality of life, work absenteeism and presenteeism, and use of healthcare resources. Process measures will assess intervention “dose”, website usage, and intervention fidelity. An economic evaluation will be conducted from the National Health Service, employer and retailer perspective using both a cost-utility and cost-effectiveness framework. The inclusion of a discrete choice experiment will further generate values for a cost-benefit analysis. Participant focus groups will explore who the intervention worked for and why, and interviews with retailers will elucidate their views on the sustainability of a public health focused loyalty card scheme.

**Discussion:**

The study is designed to maximise the potential for roll-out in similar settings, by engaging the public sector and business community in designing and delivering the intervention. We have developed a sustainable business model using a ‘points’ based loyalty platform, whereby local businesses ‘sponsor’ the incentive (retail vouchers) in return for increased footfall to their business.

**Trial registration:**

ISRCTN17975376 (Registered 19/09/2014).

**Electronic supplementary material:**

The online version of this article (doi:10.1186/s12889-016-3244-1) contains supplementary material, which is available to authorized users.

## Background

The current global physical inactivity ‘pandemic’ [1] requires a determined, innovative response with a particular emphasis on behaviour change maintenance in light of the modest, short term results of interventions to date [2–4]. Interventions in the workplace have the potential to contribute significantly to the formation of behaviour change maintenance [5]. However, there has been an expansion of sedentary occupations, with less than 1 % of adults in Northern Ireland doing at least 10 min of physical activity at work per week [6]. As well as benefitting the physical and mental health of employees, workplace physical activity interventions have the potential to benefit the organisation, through reduced absenteeism and increased productivity; and the wider economy as a whole by keeping people economically active for longer [7]. If such improvements to health are realised, they could lead to lower healthcare utilisation and costs [8]. The costs of lost productivity are estimated to be £5.5 billion a year from sickness absence and £1 billion a year from the premature death of people of working age [7].

Indeed, recent NICE guidelines recommend the promotion of physical activity in and around the workplace, particularly through walking and cycling [4]. However, current evidence to support the effectiveness of such interventions is mixed [9], with reviews [10–12] calling for more robust research on workplace interventions and well-designed RCTs. Previous meta-analyses of workplace physical activity interventions have shown small, positive, short term effects [10–12] on levels of walking but little long term effectiveness is evident [4]. Thus there is a recognised need to develop workplace interventions purposefully designed to encourage physical activity behaviour change maintenance.

The UK and US Governments [13, 14] have encouraged the use of incentives for promoting healthy lifestyles. The use of financial incentives for health-related behaviour change has been met with some scepticism [15], although their acceptability may be contingent on various factors, such as their effectiveness, type, and the target behaviour [16]. There is evidence to support the use of financial incentives for the initiation of behaviour change, for example, smoking, substance abuse [17–20]. Further, recent research has demonstrated evidence of financial incentives for single, one-off heath behaviours, such as vaccinations [19], and encouragingly, habitual health-related behaviour change [20]. However, the evidence for their effect on other health behaviours is sparse. Some financial [21] and non-financial incentives [22] have been shown to increase levels of physical activity, at least in the short-term and mainly with respect to structured exercise programmes [22], rather than free-living physical activity. There is a wealth of evidence on reinforcement of behaviour that shows that whilst incentives may be effective at changing behaviour, the effects are unlikely to be maintained when the incentives are withdrawn in the absence of other interventions [23]. Therefore, financial incentives alone may not be sufficient to promote maintained physical activity behaviour change, but may do so when embedded within an evidence-based, theoretically-driven intervention [16]. Further, financial incentive interventions designed using behavioural economic concepts have been shown to be effective for changing behaviour [24]. There is also limited evidence around the cost-effectiveness of interventions to promote physical activity in the workplace [25, 26], or indeed the cost-effectiveness of financial incentive-based interventions [19]. Therefore, to address such gaps in the evidence base and following the successful completion of a pilot study [27], we aim to conduct a cluster RCT of a complex intervention incorporating financial incentives to encourage physical activity and maintained behaviour change.

## Research objectives

The cluster RCT has the following objectives:To investigate the effectiveness of the intervention to increase employee’s physical activity levels;To investigate if any change in physical activity behaviour is maintained over time;To conduct cost-effectiveness, cost-utility and cost-benefit analyses of the intervention;To investigate how the intervention impacts on other health behaviours and outcomes;To investigate wider work-related effects including sickness absenteeism and work presenteeism;To investigate the mediators of (a) uptake and use of the loyalty card, (b) initiation, and (c) maintenance of behaviour change;To conduct a parallel qualitative study to further identify those who benefitted from the intervention, how and why it worked for them, and explore mediators of behaviour change;To conduct a Discrete Choice Experiment (DCE) to investigate the possible effective levels of incentives for such interventions;To conduct a behavioural economic field experiment on inter-temporal and risk preferences to investigate the relationship between behavioural change, discounting and financial incentives.

## Methods/design

### Design

A workplace-based cluster RCT will evaluate the intervention, incorporating nested behavioural economic experiments, and process evaluation. The study protocol is developed using the MRC framework for complex interventions [28] and SPIRIT guidelines [29] and was successfully tested in a pilot study [27].

### Study population

#### Recruitment of workplaces

The study will target public sector employees involved in predominantly office-based occupations whose workplace is within Belfast or Lisburn City Centres, Northern Ireland. People in predominantly office-based jobs spend a large proportion of their day physically inactive while public sector organisations have been reported to have higher sickness absence rates than private sector workplaces [7, 30, 31]. Public sector organisations will be purposively sampled within 2 km radius of the city centre or offer similar physical activity opportunities within a 2 km radius of their location, have a minimum of 100 employees in predominantly office-based occupations, and have similar opportunities for physical activity in the vicinity of the workplace. Meetings will be held with senior management of these organisations to explain the purpose of the study and the practicalities involved if the study were to be implemented within the organisation.

#### Recruitment of participants

Recruitment methods will include email invitation to employees and posters placed around each workplace advertising the study. Emails and posters will include the website address and a web-link will be added to the organisations’ intranet sites (previously tested in our pilot study [27]). Potential participants will be able to access further information (including the Participant Information Sheet) and register their interest to participate on the study website.

Potential participants will be asked to complete a screening questionnaire via the study website or by telephone, to confirm their eligibility, based on the following inclusion criteria: based at recruited worksite at least 4 h/day (within core hours of 8 am-6 pm) on at least 3 days/week; current contract lasts for duration of the study (i.e.18 months) (to exclude temporary workers); access to internet at work; able to give informed consent; able to communicate in English; no self-reported recent history of myocardial infarction or stroke or physical limitations that would limit ability to participate in physical activity (assessed using the Physical Activity Readiness Questionnaire) [32].

All participants who meet the eligibility criteria and consent to participate will be contacted by a member of the research team by telephone or email to complete the baseline assessment. Following this, clusters of participants will be randomised to the Intervention or Control Group using computer generated random numbers. Clusters have been defined as the smallest organisational unit (e.g. a department or office/floor) within each participating workplace.

### Randomisation

A random allocation sequence will be drawn up by the trial statistician and group allocation placed in sequentially numbered, sealed opaque envelopes. Group allocation will be stratified to ensure similar numbers of clusters in the Intervention and Control Groups in each participating organisation.

### Intervention

#### Intervention group

The Physical Activity Loyalty (PAL) scheme is a complex multi-component intervention based on concepts similar to those that underpin a high-street loyalty card aimed at encouraging repeated behaviour (i.e. loyalty) [24] and is designed to incorporate a range of behaviour change techniques. Components include the provision of ‘points’ and rewards (financial incentives) contingent on meeting targeted physical activity behaviour goals (extrinsic motivation, goal-setting). Participants will be encouraged to undertake 150 mins/week of physical activity which is in line with current guidelines [33]. The PAL scheme integrates a novel physical activity tracking system with web-based monitoring and evidence-based behaviour change tools (i.e. self-monitoring, goal-setting). The proposed 6-month intervention will involve placing sensors (wifi beacons) in the vicinity of participating workplaces at specific locations to encourage physical activity within a 2 km radius of participants’ worksites (see Fig. 1) (i.e. provision of prompts/cues, habit formation, addition of objects to the environment). Locations include along footpaths, local parks, leisure centre, shopping mall, bus stops and train stations. Maps of various walking routes and details about physical activity opportunities tailored to the workplace will be provided on the study website (instruction on how to perform behaviour) [34]. Participant’s activity will be logged when they pass within an approximate 25 m radius of the wifi sensors with their PAL keyfob when undertaking physical activity (e.g. walking). This logs the place, date and time of the bout of activity. Participants can log onto their account on the study website and receive real-time feedback on minutes of their physical activity. Minutes will be converted to ‘points’ (10 ‘points’ for 1 min of activity recorded), and collected ‘points’ are redeemable for rewards (downloadable retail vouchers) sponsored by, and redeemable at, local businesses. To reduce the risk of ‘gaming’, a daily ‘points’ cap will be implemented and the transit times between sensors checked for anomalous values [27]. Bonus rewards and ‘Double Points Days’ will be offered when participants meet specific weekly physical activity targets. [17].

**Fig. 1 Fig1:**
[figure not shown]
Physical activity monitoring system

To tailor the intervention, a purposive sample of employees (both men and women across a range of ages) will participate in three focus groups (maximum 10/group) prior to the intervention to explore aspects such as the availability of, and preferences for opportunities for physical activity proximal to the workplace. Sensor locations will be determined from the feedback received in the focus groups regarding popular walking routes. Employees’ opinions on the website interface and the rewards redemption function, for example, will also be considered. To determine incentive levels we will use stated preferences of the participants from the DCEs to assess their mean Willingness to Accept (WTA), Willingness to Pay (WTP) and the trade-offs they would make for the attributes [35] of the incentive programme, prior to the intervention. This information will help us determine the level of the rewards available for earned ‘points’ (further detail below).

In addition to the financial incentive element, the intervention has several other components designed to enhance the effectiveness of the incentives as advocated by Marteau et al. [17]. These components are delivered via the study website and designed to have multiple effects: (a) to increase usage of the study website, (b) as effective Behaviour Change Techniques (BCTs) in their own right, and (c) as techniques designed to aid the transition from more extrinsically motivated behaviour to more intrinsically motivated habitual behaviour. The techniques include the provision of regular tailored motivational emails, tailored feedback, information on walking routes in the vicinity of the participating workplaces and links to other resources such as physical activity advice and healthy eating guidelines. It also includes self-regulation techniques of goal setting, self-monitoring, and prompts to behaviour [36].

#### Underpinning theoretical framework

The financial reward component of the intervention is based on principles of Learning Theory by providing an immediate reward (extrinsic motivation) for behaviours that offer health gains in the future. It also contains elements based on other approaches, such as goal setting, prompts, self-monitoring, and habit formation which fit within a self-regulation control theory framework [37], motivational messages (persuasion), and social support (vicarious experience) which should increase self-efficacy according to Social Cognitive Theory [38]. Social Cognitive Theory also holds that satisfaction with the consequences of behaviour change can act as a reinforcing mechanism, in addition to the reinforcement of financial rewards. Thus, the financial incentive component is embedded in a complex intervention containing evidence-informed BCTs, as previously advocated [17]. Figure 2 presents the logic model underpinning the intervention development.

**Fig. 2 Fig2:**
[figure not shown]
Logic Model of the Physical Activity Loyalty Scheme

#### Control group

Those assigned to the waiting-list control condition (n = 388) will be offered the opportunity to participate in the intervention after the 18-month follow-up period. Participants in this group will complete outcome measures at the same time ‘points’ as the Intervention Group.

### Outcome measures

All outcome measures will be analysed and, where required, collected by a Postdoctoral Research Fellow (PDRF) blinded to group allocation. Self-reported outcome measures will be collected at baseline, 6 months and 18 months (unless otherwise stated), via online questionnaires distributed by email and automatically collated via Qualtrics (www.Qualtrics.com) (successfully employed in our pilot trial [27]).

#### Physical activity

The primary outcome is mean steps/day objectively measured by a sealed pedometer (to blind participants to the output) worn on the waistband (Yamax Digiwalker CW-701, Japan), for which reliability and validity has been established [39–41]. Participants will wear the pedometer for 7 consecutive days, complete a wear time diary, and the Global Physical Activity Questionnaire (GPAQ) to elucidate the context of activity undertaken [42]. These measures will be collected at baseline, 6 (immediately post-intervention), 12 (6 months post-intervention) and 18 months (1 year post-intervention). This schedule ensures that we can account for the impact of seasonality of physical activity behaviours on the intervention effect.

#### Health and wellbeing

Secondary outcome measures of health (Short Form-8 (SF-8)) [43], Quality of Life (EQ-5D-5 L) [44–46], and well-being (Warwick-Edinburgh Mental Wellbeing Scale (WEMWBS)) [47, 48], are included. Items from the SF-8 questionnaire can be derived to give an indication of both physical and mental health. The WEMWBS comprises 14 positively worded statements, where scores are summed with higher scores indicating greater mental well-being. The EQ-5D-5 L questionnaire is a health state utility measure based on five dimensions of mobility, self-care, usual activities, pain/discomfort, and anxiety/depression, and a visual analogue scale (0–100) EQ-5D-5 L index-based values (utilities) derived from a crosswalk study are then applied to the EQ-5D-5 L levels to translate changes in health states to Quality Adjusted Life Years (QALYs) for use in cost-utility analysis [45].

#### Work-related impacts

Specific questions from the WHO Health and Work Performance Questionnaire [49] will be used to measure work presenteeism (measurable extent to which physical or psycho-social symptoms and conditions adversely affect the work productivity of those in work [50]). This validated method comprises three questions with answers on an 11-point Likert scale asking participants to rate their job performance levels, and has been demonstrated to be sensitive for detecting change following a physical activity intervention [51]. Work absenteeism will be measured by asking participants to state the number of day’s sick leave in the past 6 months and will be verified objectively by each organisations’ Human Resource Department where possible.

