From the public sector perspective, the analysis will involve firstly generating ICERs using healthcare utilisation data and EQ-5D data. Secondly, from the employer’s perspective, the effect of physical activity on absenteeism will be used to estimate potential cost savings to employers (absenteeism model); and thirdly, we will employ an algorithm to translate changes in EQ-5D into quantifiable changes in productivity (productivity model [89–91]). Individual EQ-5D scores at baseline, 6 and 18 months will also be converted into estimated levels of productivity using this algorithm and the total productivity gain over 6 and 18 months for each group will be calculated. To calculate the ICER, from an employer’s perspective, the additional costs will be divided by the additional gain in total employee productivity by the Intervention Group.

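### Sick-leave recall misses months 6 to 12, so any 18-month absence total or employer saving needs an assumption, and the saving is worded around physical activity and not the randomised difference

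*Protocol article*

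**What the plan says.** All references are to the protocol article.

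- **Default schedule (Outcome measures):** "Self-reported outcome measures will be collected at baseline, 6 months and 18 months (unless otherwise stated").
- **Sick leave (Work-related impacts):** participants give their days of "sick leave in the past 6 months and will be verified objectively by each" organisation's "Human Resource Department where possible". No other schedule is stated for this item.
- **The 12-month contact (Physical activity):** for the pedometer, the wear diary and the activity questionnaire, "These measures will be collected at baseline, 6 (immediately post-intervention), 12 (6 months post-intervention) and 18 months (1 year post-intervention"). Sick leave is not among these measures.
- **Length of the randomised comparison (Control group):** control participants "will be offered the opportunity to participate in the intervention after the 18-month follow-up period".
- **Randomised analysis (Statistical analysis):** the primary mixed model, run at 6 months and again at 18 months, is repeated for the work-related outcomes (Objective 5).
- **Employer saving (Economic analyses):** "the effect of physical activity on absenteeism will be used to estimate potential cost savings to employers (absenteeism model"). A separate productivity model converts EQ-5D scores, and for that model "the total productivity gain over 6 and 18 months for each group will be calculated".

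**The concern.** Sick leave is a count that builds up over time. A total for a period can be formed only if the recall windows, or another source, cover the whole period. Here the recall length (6 months) is shorter than the interval between the last two questionnaires (12 months), so a block of follow-up goes unasked. That block starts on the day the incentives end, and whether any effect survives that point is the maintenance question the trial sets itself.

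The second issue is what the employer saving is built from. Physical activity is measured after randomisation. Illness can reduce walking and cause absence together, so an effect of activity on absence does not inherit the protection of randomisation. The trial will already hold a comparison that does.

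At stake is one component of the economic evaluation (Objective 3) and the cumulative reading of a secondary outcome (Objective 5). The primary outcome is not touched.

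**Working it through.** The article gives no figure of its own to reproduce here, so the check is on coverage.

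**1. Inputs.** Recall length 6 months (Work-related impacts). Questionnaires at months t = 0, 6 and 18 (Outcome measures). Intervention in months 0 to 6, randomised comparison in months 0 to 18 (Intervention group; Control group). Month 0 is taken as baseline and start of intervention.

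**2. Windows.** A questionnaire at month t covers t - 6 to t.

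| Questionnaire | Window covered |
|---|---|
| Baseline | -6 to 0 |
| 6 months | 0 to 6 |
| 18 months | 12 to 18 |

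**3. Gap.** Months after randomisation that are covered: 6 + 6 = 12 of 18. Uncovered: months 6 to 12.

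- Share of follow-up: 6/18 = 33%.
- Share of the post-intervention year: 6/12 = 50%.

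**4. What can be estimated.** Let d1, d2 and d3 be the between-arm differences in sick days in months 0-6, 6-12 and 12-18. The questionnaires estimate d1 and d3, each over a fully observed window. The 18-month total is d1 + d2 + d3, and d2 is not observed. The values below are assumed, solely to show that the observed part does not determine the total; the article gives no absence rates.

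| d1 / d2 / d3 (days, assumed) | Total | Observed, d1 + d3 | Share missed |
|---|---|---|---|
| 0.5 / 0.5 / 0.5 | 1.5 | 1.0 | 33% |
| 0.5 / 0.5 / 0 | 1.0 | 0.5 | 50% |
| 0.5 / 0 / 0 | 0.5 | 0.5 | 0% |

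The last two rows give identical questionnaire data and different totals. Interpolating d2 as (d1 + d3)/2 = 0.25 gives 0.75 for both, which is right for neither.

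**5. Season.** Months 0-6 and 12-18 are 12 months apart and so fall in the same calendar half-year for a given participant. The only recall window in the opposite half-year is the baseline one, which precedes randomisation and carries no information on the intervention effect. Interpolation would therefore also assume that the difference does not vary by season.

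**6. Basis of the saving.** Set side by side, Statistical analysis yields a between-arm estimate for work-related outcomes, the productivity model in Economic analyses is totalled by randomised group, and the absenteeism model in the same section is tied to the effect of activity on absence. Only the last is not expressed as a comparison of groups.

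**7. After the change.** Adding a 6-month question at month 12, or covering months 6 to 18 in one recall at month 18, raises coverage from 12 to 18 of 18 months. So do employer records for months 0 to 18, if complete. No money value can be computed, because the article gives neither absence rates nor a daily cost.

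**The case against.** The strongest reply is that the plan does not promise what the gap would spoil. Objective 5 is met by comparing six-month sick leave at 6 and at 18 months, and both windows are complete and randomised. This stands. A reader might infer that the sick-leave outcome itself is invalid; the text does not support that.

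A reader might also infer that the absenteeism saving is declared over 18 months. It is not. The phrase about 6 and 18 months belongs to the EQ-5D productivity model, and no horizon is given for the absenteeism model. That difference matters: EQ-5D is a state at a time point and can be interpolated between visits by convention, while a count over a window that nobody asked about cannot be recovered in the same way.

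Third, employer records might already span the gap. The extraction period is not stated, and a condensed article may leave it to the full protocol. So it cannot be said that months 6 to 12 will certainly go unobserved. As written, however, the records serve to verify the recalled counts, and only where possible, so they cannot be relied on to fill the gap.

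Fourth, the phrase about physical activity could be loose wording for the effect of the intervention. No estimator is given, so it would go too far to say that the saving will come from an observational association. What stands is that the words, taken literally, name a quantity that randomisation does not protect, and that nothing in Economic analyses links the saving to the between-arm estimate.

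Finally, interpolation with a sensitivity analysis is available. It is an assumption about the missing period and does not replace data from it.

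**Conclusion.** The point holds in a limited form. On the stated schedule and recall length, self-reported sick leave leaves months 6 to 12 uncovered: 33% of follow-up and half of the period after the incentives end. Any cumulative 18-month absence difference or employer saving would rest on an assumption for those months. The wording of the absenteeism saving should also be tied to the randomised difference, which the plan already estimates.

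This rests on two readings: that the default questionnaire schedule applies to sick leave, since no other is stated, and that employer records are limited to checking the recalled counts. A full-period extract of those records would close the gap. The size of any error in days or money cannot be derived from the article; the figures assumed above only show that the total is not determined. The six-month arm comparisons and the primary analysis are unaffected. The change is worth making because it is cheap, but the issue is confined to a secondary outcome and one part of the economic evaluation.

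**What to change.** 1. **Close the window.** Add the same sick-leave item to the existing 12-month contact. Alternatively, request absence counts from the employers for the whole of months 0 to 18, so that the records do more than check the recalled periods. If the 12-month contact has passed, ask for the preceding 12 months at the 18-month questionnaire.
2. **Reword the saving.** State that the absenteeism model uses the between-arm difference in absence days, and state the horizon to which it applies.
3. **If the gap stays open,** report the absence differences for months 0-6 and 12-18 separately. Label any 18-month total as dependent on an assumption for months 6-12, and show a range.

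Cost: one question at a contact that already takes place, with slight extra participant burden, or a wider request to the human resources departments, some of which may not be able to supply it. The 12-month recall option brings more recall error. Basing the saving on the between-arm difference needs no further data beyond closing the window.
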